## Abstract

Older carers (≥50 years) of older people (≥65 years) are an important sub-group of carers performing valuable roles in providing informal care but often do not have the time or give priority to supporting their own health and wellbeing. Current services supporting older carers’ health and wellbeing are fragmented and inadequate. Through previous research and co-design activity by our team, an innovative multidisciplinary Carer Health and Wellbeing Service (CHWS) has been developed. The purpose of this protocol paper is to describe the rationale for the CHWS and the methods proposed to evaluate its effectiveness and implementation outcomes. The CHWS commenced in March 2024 at Peninsula Health, Melbourne, Australia. Older carers of older people can be referred from multiple sources, including self-referral. A pre-post mixed methods study design is being utilised. Initial assessments include the Carer Support Assessment Needs Tool (CSNAT) and carer prioritisation of their needs, which guides further assessment and interventions. Assessments will occur at Service intake and 6 months later. The primary effectiveness outcome is the Preparedness for Caregiving Scale, and primary implementation outcomes are reach and adoption. Interviews of carers, referrers and staff, and a cost-utility analysis will be undertaken. The target sample size is 137 carers undertaking assessment and intervention over the 15 months data collection. Generalised linear regression will be used to compare pre- and post-continuous outcome measures. Qualitative data will be thematically analysed. Results will inform future scaling up of this innovative approach to optimising health and wellbeing of older carers of older people.

**Trial registration number:** Australian New Zealand Clinical Trials Registry (ANZCTR) – ACTRN: 12625000245493.

## Introduction

Caring for an older person with care needs is usually a progressive role, where care needs often increase in number and complexity over time [1–3]. A growing proportion of carers of older people are older persons themselves [4], many of whom have multiple and increasing health problems of their own [5,6]. These carer health problems can impact their physical and mental health and quality of life and frequently contribute to increasing care support challenges over time [2,7]. Although some informal carers of older people report positive experiences associated with their caregiving role, many report significant negative impacts to their health and wellbeing [5,8,9] that may also compromise their ability to sustain the provision of informal care longer term. Sustainability of the caregiving role and maintenance of quality of life for older carers of older people is therefore dependent on having adequate support and on being able to optimally manage their own health and wellbeing.

Much of the research about carers includes carers of all ages, with little focus specifically on older carers [10], although almost half of carers in Australia are aged 55 years or older [4]. While some generic factors affect health and wellbeing of carers of all ages, additional factors and potentially different intervention approaches may be more relevant and effective for older carers. A survey of 189 older carers of older people in Australia indicated that their quality of life was moderately reduced, with 35% indicating their own health issues were a barrier to supporting their older family members [11]. Eight in ten older carers had informed their general practitioner that they were carers, or had discussed their caring role and needs with their general practitioner, however, only 46% reported receiving advice for, or support with, their role as carers. Factors associated with better quality of life for carers included specialist clinics providing advice/assistance with the caring role [11]. While 58% attended specialist clinics with their care recipient, only 19% received specific advice or support to manage their own health and their carer role. Unpublished research from the same project [11] incorporating staff interviews at specialist geriatric out-patient services corroborated similar unmet needs for older carers of older people.

There is research evidence that single intervention approaches can improve health and wellbeing outcomes for carers (including carers of older people) [12], e.g. psychosocial programs [13,14], physical activity/exercise [15–19], occupational therapy programs [20], goal setting [21], and respite care [22]. Multi-component interventions (combining two or more approaches) have also been effective [23–25]. Despite these research findings, translation of these approaches into routine practice is currently limited and fragmented, and few of these interventions focus specifically on older carers of older people. More commonly, the focus of health professionals’ attention, and the person who is usually interacting with health services for assessment and intervention, is the care recipient (not the carer). There is little research evidence detailing systematic and dedicated assessment of the needs and supports to enhance health and wellbeing of older carers of older people, or implementation research evaluating translation of this research into practice.

One report (an unpublished Master’s thesis) is the only literature identified that reports a specialist service targeting older carers of older people [26]. This Carer Clinic model operates in Sao Paulo, Brazil, and targets carers aged ≥55 years of age. The clinic’s multidisciplinary team consists of a social worker, psychologist and physician, who provide multi-disciplinary assessment and interventions, focussing on medical, social and psychosocial aspects of carers’ needs. No formal evaluation of the outcomes of this novel service has been published.

There is a need for a systematic approach to identifying and supporting older carers of older people to optimise their own health and wellbeing while sustaining their caregiving role [27]. We have undertaken recent research activity with key stakeholders, that included voices of older carers, carer support organisations, health professionals, health care organisation administrators, policymakers, and researchers with expertise in health and wellbeing of older carers, to co-design the development of a novel Carer Health and Wellbeing Service (CHWS) in Melbourne, Australia [28]. Key elements of the model of care determined through the co-design panels included being: (1) driven by carer-identified needs and priorities; (2) interdisciplinary, with flexibility in initial screening and subsequent tailoring of assessments and interventions to ensure relevance to individual carers (including referral to other services if required); and (3) able to provide multiple modes of service delivery and resources, including face-to-face, telehealth (supporting those with difficulty leaving home, or in regional/rural areas) and website resources [28].

This protocol paper details the methods being used in the implementation of the new CHWS and evaluation of the impact of the service on the health and wellbeing of older carers (for this study, defined as carers aged 50 years or older) of older people (defined as people receiving informal care aged 65 years or older). This study aims to evaluate (1) the effectiveness outcomes for older carers participating in the CHWS; (2) the implementation outcomes associated with the CHWS – including feasibility, reach, acceptability (carers, Service staff, referrers), maintenance and fidelity; and (3) the cost-utility of the CHWS.

## Methods

A mixed methods one-group pre-post (6-month) study design will be utilised, using both quantitative and qualitative data. The protocol follows the checklist and guidelines described in the SPIRIT guidelines for the content of clinical trial protocols (Fig 1, and Supporting Information S1 Checklist) [29] and the ‘Template for Intervention Description and Replication (TIDieR) (Supporting Information, S2 Checklist) [30]. The project commenced recruitment on March 1 2024, recruitment will end on 31 May 2025, and the project will end in December 2025. The study was retrospectively registered in the Australian New Zealand Clinical Trials Registry (ANZCTR; number ACTRN: 12625000245493). The delay in study registration, which occurred after the commencement of participant enrolment, was primarily associated with the complexities of establishing a new service within a health service and its requirements; and a six week delay in early 2025 when the trial registration site was closed due to a cyber security incident. The authors confirm that all ongoing and related trials for this intervention are registered.

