**Fig 2 pone.0326363.g002:**
[figure not shown]
Referral, assessment and intervention processes for the Carers Health and Wellbeing Service (CHWS).

a)Description of CHWS purpose and processes (if not provided by the referrer to the carer);b)Screening demographic questions and questions to ensure the carer meets the inclusion criteria for participating in the CHWS;c)Description of the option for participation in the research study and their participant data being used as part of the CHWS evaluation (and the need for signed informed consent for this to occur) (Note: consent to participate in the research is not a prerequisite to use the CHWS services, so those not providing consent for the research will still work through all the CHWS processes, but the research team will not have access to their data);d)Introduction to the CSNAT, and request for the carer to review and reflect on the CSNAT questions in preparation for the initial CHWS assessment (which will be the same process whether it is conducted face-to-face or online);e)Carers’ initial perception of the main area/s they are seeking assistance, information, advice or interventions to assist them to maintain or improve their own health and wellbeing (to guide decision-making by CHWS staff regarding the most appropriate team member (discipline) to conduct the initial assessment – this will be accommodated as best as possible based on information provided and availability of the relevant staff member). Adjustments may be made in terms of the CHWS staff member to undertake the initial assessment to minimise delays in commencement with the services if required; andf)Preferred mode of Service participation (in-person or online), and preferred mode for receiving information from the Service (email, phone, post).

The carer’s first appointment will be scheduled where possible with the CHWS staff member whose professional expertise best aligns with the primary needs identified by the carer during screening. This staff member will be designated the carer’s key contact person, who will assume overall primary contact and oversight of the carer’s CHWS management. The first appointment will have a focus on: completing all core assessments (Table 1); identifying prioritised carer needs (up to three top prioritised needs, based on the carer views in the context of the CSNAT and any other needs); and shared decision-making regarding initial area/s to address and intervention/s (what matters most).

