**CORE ASSESSMENTS**	
Carer Support Needs Assessment Tool (CSNAT) [31,35]^*^.	The CSNAT is a 14-item tool (seven domains of support enabling the carer to care, and seven domains of support relating to their own wellbeing), used to obtain information on and prioritise carer’s support needs. It can be used as both a research tool and as part of a practice intervention (staff using the CSNAT will undergo required training). *The CSNAT will not be used as an outcome measure, as recommended by the tool developers.*
Preparedness for Caregiving Scale (PCS) [34]^*^.	**Primary outcome measure.** The PCS includes eight items evaluating how prepared carers consider themselves to be for different aspects of caregiving. Each item is rated on a five-point scale (0 = not at all prepared; 4 = very well prepared). Higher scores indicate better preparedness for caregiving. Components of the PCS and overall PCS score have been shown to be responsive to change in a nurse-led intervention for family carers of older people being discharged from hospital [36].
EuroQoL Five Dimension Five Level scale (EQ-5D-5L) [37]^*^.	The EQ-5D-5L is a widely utilised measure of quality of life that is also used in health economic evaluations. For this study, the five domains of the EQ-5D-5L (mobility, self-care, usual activities, pain/discomfort and anxiety/depression) will be assessed, each on five levels (no problems, slight problems, moderate problems, severe problems and extreme problems).
Family Appraisal of Caregiving Questionnaire (FACQ) [38]^*^.	The FACQ has 26 items, rated on a 5-point scale ranging from 1 (strongly disagree) to 5 (strongly agree). The 26 items are grouped into four subscales, including: caregiver strain, positive caregiving appraisals, caregiver distress, and family wellbeing.
Health economics survey to capture care related data and health care utilisation data including emergency department and hospital admissions over the past 6 months^*^	This survey will ask average weekly hours of care provided by the carer, by other people who are not paid, and by other people who are paid; as well as capture the “preferred” and “actual” weekly hours the carer spends on their top three leisure activities (where the carer role contributes to the gap between “preferred” and “actual” hours of participation). It will also include self-report health care utilisation information. This information will be used in the cost utility analysis.
**BESPOKE ASSESSMENTS** ^**^	

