Assessments will occur at initial intake assessment, and 6 months later, as the Service will operate typically with a 6 month episode of care. However, for carers who feel their needs have been fully met earlier than 6 months, the final assessment will be brought forward. For carers who may still have active issue/s being worked on with staff, a 6 month assessment will be completed (to be used in main data analysis), and a final assessment undertaken at a later time point when the episode of care is completed.

Depending on the identified carer prioritised needs and shared decision-making, the CHWS staff member (or another staff member if more relevant) will undertake one or more additional bespoke assessments related to the area/s of need identified. For example, if the areas of need related to depression and poor sleep, additional assessments could include the 21-item (short form) Depression, Anxiety and Stress Scale (DASS-21) [39,57], the Insomnia Severity Index (ISI) [49], and the Epworth Sleepiness Scale (ESS) [50]. Table 1 lists the main bespoke assessment tools that will be utilised depending upon the prioritised needs of the carer. Additional assessment tools may be selected by the CHWS staff member if a domain of interest is not covered by the bespoke tools listed in Table 1.

As well as the core and bespoke (individualised) assessment tools used for each carer, the Client Satisfaction Questionnaire (8-item, CSQ-8) will be completed by all carers [58]. Additional client satisfaction questions will evaluate carer perspectives of the CHWS referral processes, carer needs prioritisation processes, assessments, interventions, interactions and communications with CHWS staff, modality of interactions with CHWS (face to face or online, or hybrid/ mix), referrals from CHWS and communications with other relevant medical or health professionals, access to relevant information and resources, timeliness of processes and communications, and what they considered worked well and what aspects did not work well. The CSQ-8 and additional service satisfaction questions will be available online (through Qualtrics) or in hard copy. The additional satisfaction questions will be rated using a 7-point Likert scale response, as well as some open-ended questions.

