a)*Reach* will be determined through referrals received, aiming for >80% of appointment slots for all CHWS staff being utilised in the last six months of the study recruitment period; and overall sample size relative to the planned sample size (see analysis and sample size calculation section). Sources of referrals (medical practitioners, allied health professionals, carers themselves) will be reported;b)*Effectiveness* outcomes will mainly include the carer outcome measures (Table 1), and also a *cost-effectiveness* evaluation. A cost-utility analysis will be conducted using a societal perspective over a 12 month time horizon (6 months before the carer’s first appointment and 6 months following the carer’s first appointment). Cost data will include CHWS intervention costs (excluding research costs); carer emergency department presentations and hospital admissions (self-report); the quantity of care provided to the person requiring care, including average weekly hours of care provided by the carer, by other people who are not paid, and by other people who are paid (self-report). In addition, the carer will report the “preferred” and “actual” weekly hours spent on their top three leisure activities (noting when the carer role contributes to the gap between “preferred” and “actual” hours of participation). Effect data will be based on the utility index derived from the EQ-5D-5L [37], measured during the carer’s initial appointment and again at their 6 month follow-up assessment. The change in utility index between initial assessment and 6 months will be used to determine quality-adjusted life years (QALYs) gained or lost by the carer. Cost and effect data will be combined to determine incremental cost-effectiveness ratio (ICER) per QALY gained, with a threshold of <$AUD50,000/QALY gained to determine cost-effectiveness [55].c)*Adoption* will be evaluated through several service system outcomes (percentage completing intervention programs and 6 month assessment, number of interventions undertaken, and number of intervention sessions undertaken with CHWS staff). Acceptability of the service will be evaluated through the CAQ-8 and associated survey items, and interviews of a purposive sampling of carers (after the 6 month assessment), service referrers, and an interview with consenting CHWS staff in the last six months of the intervention, or an exit interview for staff leaving the service;d)*Implementation* includes fidelity of the program as intended (which will be evaluated by members of the research team reviewing 5% of de-identified patients’ assessments and intervention programs implemented against CHWS protocol) and adaptations (CHWS staff will document issues and adaptations made during the CHWS implementation and report these to the research team; and will be asked to comment on adaptations in the staff interviews). Other service-related aspects of implementation will be captured as part of the economic evaluation (e.g., costs, non-attendance at booked sessions);e)*Maintenance* at the individual (carer) level will be evaluated through the proportion of carers completing the 6 month assessment and completing interventions. At the system level, maintenance will be determined through the CHWS being able to continue beyond its initial two year intervention period.

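### The uncontrolled intake-to-6-month change is used as effectiveness and as QALYs gained, which sets the background change to zero without saying so

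*Protocol article*

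**What the plan says.** All references are to the protocol article.

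- **Design (Methods).** "A mixed methods one-group pre-post (6-month) study design will be utilised, using both quantitative and qualitative data". No control group, external reference or untreated course is described.
- **Measurement times (Procedure: Service screening and assessment tools).** "Assessments will occur at initial intake assessment, and 6 months later". The final assessment can come earlier for carers whose needs are met, but there is only one pre score.
- **Purpose (Introduction, aims; Data analysis).** The first aim is effectiveness outcomes for participating carers, with the PCS as primary effectiveness measure. Initial and 6-month scores are compared by generalised linear regression.
- **Economic rule (Implementation outcomes, item b).** "The change in utility index between initial assessment and 6 months will be used to determine quality-adjusted life years (QALYs) gained or lost". The resulting ratio is judged against AUD 50,000 per QALY. The horizon is 12 months, starting 6 months before the first appointment, but utility is measured only at the first appointment and 6 months later.
- **Expected course (Introduction).** "Caring for an older person with care needs is usually a progressive role, where care needs often increase in number and complexity over time".
- **CSNAT step (list under Fig 2, item d).** The orientation contact includes a "request for the carer to review and reflect on the CSNAT questions in preparation for the initial CHWS assessment". The core assessments, among them the PCS and EQ-5D-5L, follow at the first appointment. Table 1 says of the CSNAT: "It can be used as both a research tool and as part of a practice intervention".

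**The concern.** With one group and one pre score, the observed change is the sum of whatever the service did and whatever would have happened anyway. Using that sum as the effectiveness result, or as QALYs gained, amounts to setting the second part to zero. The protocol does not state this assumption, and it sits badly with the Introduction's account of a role whose demands usually grow. On that account an unchanged score might already be a benefit. In the other direction, carers enter by referral or self-referral and name areas where they want help, so some may be measured at a low point and recover without the service.

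What is at stake is the conclusion. The Abstract says the results will inform scaling up, and the Discussion promises effectiveness outcomes to guide policy without naming this limit. If the economic rule is followed as written, it yields a cost-effectiveness verdict that the design cannot attribute to the service.

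**Working it through.** **1. The identity.** Observed change = service effect + background change. The study measures the left side only. Reading the left side as the effect means background change = 0.

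**2. What this does to the PCS result.** Inputs from Sample size calculation:

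- n = 137. The last step reproduces: 248 × 0.55 = 136.4, rounded up. The 248 itself does not follow from its weekly rates (20 weeks × (2 + 4 + 8) = 280), but that is a separate matter.
- SD = 0.57, and a mean improvement of 0.2. Both come from an earlier two-group study. The article does not state 0.2 as the gain expected here.

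Assumptions, not in the document: two-sided 5% test, equal SDs at both times, pre-post correlation r of 0.3, 0.5 or 0.7, no loss to follow-up.

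SE = 0.57 × √(2(1 − r)) / √137 = 0.0576, 0.0487 and 0.0377.

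P(significant improvement) = 1 − Φ(1.96 − m/SE), where m = true effect + background change. The background values are assumed.

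| True effect | Background change | m | r = 0.3 | r = 0.5 | r = 0.7 |
|---|---|---|---|---|---|
| 0.20 | 0 | 0.20 | 94% | 98% | >99% |
| 0 | +0.05 | 0.05 | 14% | 18% | 26% |
| 0 | +0.10 | 0.10 | 41% | 54% | 76% |
| 0.20 | −0.10 | 0.10 | 41% | 54% | 76% |
| 0 | +0.20 | 0.20 | 94% | 98% | >99% |
| 0.20 | −0.20 | 0 | 2.5% | 2.5% | 2.5% |

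A change of 0.2 would be detected well, so precision is not the problem. The third and fourth rows are identical: a useless service with a mild upward background and a useful one with a mild downward background give the same data.

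**3. What it does to QALYs.** With linear change over 6 months, QALY gain = 0.5 year × 0.5 × (ΔU − b) = 0.25 × (ΔU − b), where ΔU is the observed utility change and b the background change. For an illustrative ΔU of +0.02:

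| b over 6 months | QALYs | Worth at AUD 50,000 |
|---|---|---|
| 0 (the plan's implicit case) | 0.005 | AUD 250 |
| −0.02 | 0.010 | AUD 500 |
| +0.02 | 0 | AUD 0 |

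So each 0.02 of background change moves the acceptable incremental cost by AUD 250 per carer. The article does not state linear interpolation. If the whole change were credited for the full 6 months, 0.02 would be 0.02 × 0.5 = 0.010 QALY, or AUD 500.

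For incremental cost C per carer, the verdict flips at b* = ΔU − C / (0.25 × 50,000) = ΔU − C / 12,500. The documents give no C, so b* cannot be evaluated now. It can be once the data are in.

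The planned 5,000 bootstrap replications do not cover this. They describe sampling error, and every replicate carries the same b = 0.

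**4. Order of the CSNAT and the baseline.** The request to reflect comes at the orientation contact, and the PCS at the first appointment. The baseline is therefore taken after a first exposure to the tool. At 6 months the CSNAT serves only to ask whether each prioritised need is fully addressed, partly addressed or unchanged. The order of forms within either appointment is not stated, and no effect of the CSNAT on the PCS is given.

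**The case against.** The strongest reply is that this is the known limit of any uncontrolled pre-post study. The article declares its design openly and calls the study a pragmatic evaluation of a new service. Effectiveness is also the name of a RE-AIM component. The primary implementation outcomes, reach and adoption, are untouched, and scenario runs for an ICER often sit in an analysis plan that is not shown. Much of this stands: the design is not hidden, and the within-carer change is a valid description. It does not answer the economic rule, which the article itself fixes: raw utility change counts as QALYs gained or lost and is judged against a threshold.

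It is also fair to say that the Introduction speaks of care needs rising, not of PCS or utility scores falling. That passage makes a zero background change doubtful; it does not supply a value.

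A reader might infer more than the documents support:

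- *That the CSNAT step inflates improvement.* Carers are asked to read and reflect, the 6-month question allows the answer that a need is unchanged, and no form order is given. Neither direction nor size can be stated, and no share of the cited 0.2 can be assigned to it. Table 1's remark that the CSNAT can form part of a practice intervention describes the tool; it does not show that reading the questions alters preparedness.
- *That the design is biased towards benefit.* Progressive decline would hide benefit and regression to the mean would mimic it. The net direction is unknown.
- *That a new baseline before the CSNAT is the answer.* Recruitment was to end on 31 May 2025, so most of the cohort would not have it. The orientation contact is made by the manager or administrative support, before signed consent is returned. The interval to the first appointment would also contain the CSNAT exposure, so drift and CSNAT effect could not be separated.

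**Conclusion.** The point holds as a limit on attribution. The change from intake to 6 months is sound as a description of carers who attended. It does not identify the service's effect, and the QALY figure and the AUD 50,000 verdict rest on an unstated assumption of no background change.

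The documents give no size for the bias. The illustrations depend on the assumed PCS backgrounds of ±0.05 to ±0.20, the assumed correlations and the assumed utility change of 0.02. Within them, a PCS background of +0.10 with no effect gives a significant improvement 41% to 76% of the time. Each 0.02 of utility is worth AUD 250 per carer under linear change, or AUD 500 if credited for the full 6 months. Whether that matters for the verdict depends on a cost per carer that is not yet known.

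The CSNAT ordering is secondary, with unknown size and direction. The implementation outcomes are unaffected.

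**What to change.** 1. In the aims (Introduction), Implementation outcomes item b and Data analysis, describe the result as within-carer change in carers attending the service, not as an effect attributable to it. The RE-AIM label can stay.
2. In item b and Data analysis, state that the base-case ICER assumes no background change in utility. Add scenario runs with non-zero background change, for example −0.02 and +0.02 over 6 months (an assumption). Report the background change b* at which the verdict at AUD 50,000 per QALY flips, and state the interpolation used for QALYs.
3. At the 6-month assessments still to come, give the PCS and EQ-5D-5L before the needs-addressed questions, and record that order. With recruitment ending on 31 May 2025, this reaches only the outstanding follow-ups.

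No new baseline is proposed for this cohort. The cost is a few extra ICER runs, a fixed order of forms and a more modest stated conclusion. No new data are needed.
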